### Phase I: preparation phase

The purpose of phase I was to understand how current individual care was delivered and experienced and what changes women, partners and midwives thought might improve care, taking into account contextual factors that might have an impact on the development, structure and content of a new model. The aim was also to assess whether a language-supported group antenatal care model might be appropriate and acceptable to address concerns raised about current care.

#### Initial dialogue and choosing study settings

In the municipality chosen for site 1, the number of Somali immigrants had increased fivefold during the last decade and the ANC midwives had begun to rethink how they were providing care. At the same time, there was awareness of lower ANC attendance and adverse outcomes among childbearing Somali-born women in Sweden,^8^ and a need for more appropriate explanations of ANC routines had been highlighted in interviews with Somali-born women.^33^ This prompted a dialogue between the principal investigator and the ANC midwives, outlining the possibility of evaluating an alternative model of care. The ANC clinic is located in a primary healthcare centre staffed by 10 midwives, within a public hospital located outside the city centre. It caters for approximately 75% of all pregnant women in the municipality and almost all of the pregnant immigrant women in the municipality, which in total has 50 000 residents. The majority of the Somali-born women visiting the clinic live in two areas situated approximately five kilometres away, necessitating use of a car or public transport.

At site 2, the ANC clinic is located in a family health centre in a suburb of the capital city. Close collaboration takes place between ANC midwives, social workers, child health nurses and the open playgroup located in the same building. Three ANC midwives are employed, and the target area includes two residential areas with different sociodemographics; with primarily Swedish-born residents in one area and non-Swedish born residents and second-generation immigrants in the other. Somali-born residents have lived in this area for more than 25 years, and midwives reported that most Somali-born pregnant women and families were able to communicate in Swedish. Integration of families of different cultural backgrounds is actively encouraged at the clinic. Initial discussions revealed that the midwives believed group antenatal care for women of mixed cultural backgrounds (with interpreters available if needed) would contribute positively to integration. As a result, it was agreed that integrated groups would be more appropriate and acceptable at this site.

#### Mechanisms for engagement: reference group and bicultural research assistants

A project reference group was established comprising research team members, antenatal care midwives and representatives of the Somali community from both sites. Terms of reference were developed, including provision of advice to the research team on design of the intervention, appropriate recruitment processes and data collection methods; development of study questionnaires; networking with Somali associations and ANC clinics as well as contributing to the interpretation and dissemination of findings throughout the project period.

A bilingual Somali research assistant with a healthcare background was employed full time in the project at site one. This enabled networking with Somali community members, bridging language gaps, input into questionnaire design, recruitment of participants, data collection and arranging and interpreting focus group discussions together with research team members. At site 2, focus group discussions were facilitated by two Somali community workers, including recruitment and interpreting.

#### Participatory focus group discussions with Somali parents and antenatal care midwives

To develop understanding of current antenatal care and how it was experienced, phase I included focus group discussions (FGDs) with Somali-born parents and with ANC midwives; presented in brief below and in [name] *et al*.^34^

Parents were recruited using purposeful sampling. In total, 16 mothers and 13 fathers with varied length of stay in Sweden and recent experience (<2 years) of ANC were included. Seven ANC midwives were recruited purposefully from both sites and from an additional site where the midwives had previous experience of group antenatal care with Somali-born parents.

Three focus group discussions were held with Somali-born mothers, two with Somali-born fathers and three with ANC midwives. Emerging themes were highlighted by the researchers and crosschecked during the discussions with participants for accuracy.^35 36^ Thematic analysis as described by Attride-Sterling^37^ was used to interpret data from the FGDs.

#### Key findings informing intervention development

Challenges at the system level and in the care encounter in striving for optimal ANC were identified^34^ alongside findings that could directly inform the intervention development. Instead of focusing on specific cultural or ethnic aspects of care, the results indicated a need to maintain focus on diversity and individual needs. The need for forums for social interaction, and for dialogue which could bridge gaps between midwives’ and women’s understanding of the purpose of antenatal care, improve communication and reduce the risks for stereotyping was apparent. Responding to a wide range of health literacy needs, welcoming fathers and safeguarding an open atmosphere were other issues raised. Furthermore, practical issues such as optimal location and times for ANC visits were discussed. The findings contributed valuable input to the programme theory and to the decisions regarding underpinning central principles for the coming intervention (table 1) as well as for the development of the structure and content of the intervention in phase II.

**Table 1 T1:** Logic model of Hooyo including problem statements, conceptual framework and rationale, the Hooyo group antenatal care model, hypothesised mechanisms of effect and desired outcomes

Problem statement	Conceptual framework and rationale	Hooyo: a group approach to improving ANC	Hypothesised mechanisms of effect	Desired outcomes
Current ANC in Sweden may not provide equitable care for Somali-born women: Lower participation in antenatal care Poorer birth outcomes Communication difficulties Lack of familiarity with Swedish antenatal care structures Lower attendance in parental education Negative attitudes and suboptimal care Initial FGDs with Somali-born parents/ANC midwives highlight need for: Improved communication and dialogue Bridging gaps between divergent health literacy knowledge Care free from generalisa-tions, tailored to individual needs Clearly described expecta-tions regarding partner’s role	Core values for quality care: respect, communication, community knowledge and understanding Person-centred care to identify and address women’s individual needs Continuity of care for positive care experiences and health outcomes Group antenatal care a promising alternative to individual visits: More positive views of care Some positive impacts on birth outcomes More time with midwives and more comprehensive parental education In Sweden studied with Swedish-speaking groups only Key underpinning principles: Active involvement of Somali parents/ midwives in assessment and care design Attention to language and contextual factors Flexibility in study methods to respond to issues as they arise A care model ready to continue or replicate after project ending with minor adjustments	Language supported group antenatal care involving 8–9 group sessions 1 1/2 hours with 6–8 women (partners welcome) from gest. week 24 Facilitated by two midwives assisted by interpreter Brief individual midwife check-ups incorporated Childbirth/parenting themes with focus on dialogue and discussion Motivational interviewing for groups as a vehicle for focusing care on women’s needs Adjustments based on local needs at each site: Site 1: Groups specifically for Somali-born Site 2: Groups with diverse backgrounds and languages	Interpreter-supported group dialogue facilitated by midwives will result in Improved communication →better suited care More time for discussions →mutual understandings in views around childbirth and health promotion → strategies for improving outcomes An additional arena for social contact and support →increased well-being Combining pregnancy check-ups with groups →motivation for attending ANC, and parental education Common language/ background → understanding and empower women to raise voices in having needs addressed Mixed groups →integration and understanding through cross-language/culture interactions	Women: Happier with the ANC More confident in and knowledgeable about the pregnancies Improved well-being Improved attendance at antenatal care visits Improved uptake of health advice Ultimately improved pregnancy outcomes Partners: Feeling welcomed and included Increased understanding of expectations Midwives: Improved understanding of womens needs Feel better able to share health knowledge in meaningful ways Provide more supportive, non-judgemental care Positive about benefits of group care

ANC, antenatal care; FGD, focus group discussion.

### Phase II: development of the intervention and study evaluation tools

#### Developing group antenatal care

Prior to the study commencing, a review of the literature on migrant women’s birth outcomes, experiences of antenatal care and on alternative models of care for migrant women had been undertaken, including group antenatal care. This, together with the experiences of team member EA in evaluating group antenatal care in Sweden,^19 24 27^ led us to investigate whether group antenatal care could be appropriately developed to improve outcomes for Somali-born women. The preliminary findings from the FGDs confirmed language supported gANC as a possible alternative care model, and this was discussed in the reference group. Research team members participated in discussions at each study site during these processes. The intervention development was characterised by constant modifications to fit local prerequisites at both sites, including local guidelines and routines in the ANC clinics, and needs among the women; not all of which were apparent from the start.

#### Underpinning principles

Central findings in the FGDs were the desire for individualised care, a need for forums for dialogue to address variations in health literacy and healthcare understanding and at the same time respond to the request to move beyond stereotypes based on ethnicity or ‘culture’. This led us to focus on person-centred care (PCC)^38^ as a foundation for the intervention, and on how this could be strengthened and encouraged through active dialogue in group-based care. This was also in line with the ongoing implementation of PCC generally in the health system in Sweden. In searching for a method to support this approach, the midwives proposed motivational interviewing (MI). They had already received some training in MI for use in individual appointments, and now MI for groups was added. Principles of PPC and MI encourage understanding the person as an individual and developing partnership and promoting self-efficacy for which an active and open dialogue is central.^38–40^

#### Addressing language and integration

To respond to the diverse needs identified at the two ANC clinics and to assess advantages and disadvantages with both homogeneous and heterogeneous groups regarding language and cultural background, it was decided that gANC would be offered to Somali-born women at site 1. A large number of Somali migrants had settled in this municipality in recent years, and this meant that many were not yet fluent in Swedish. At site 2, gANC would be offered to all women attending the clinic, in integrated groups. At site 1, the need for a Somali interpreter at each session was anticipated. Since a finding in the FGDs was that continuity of known Somali interpreters had been a previous success factor, it was decided to engage two experienced interpreters who could alternate. At site 2, it was anticipated that the need for interpreters in different languages would vary and thus they would be engaged when needed.

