## Methods and analysis

### Design

An intervention development and feasibility study including focus group discussions, a historically controlled evaluation and process evaluation.^29 30^ The intervention is implemented in two antenatal care clinics in mid-Sweden. The feasibility and piloting includes testing procedures for acceptability, estimating the likely rates of recruitment and retention of women and the calculation of appropriate sample sizes for future controlled trials. Complex interventions that are adjusted to local, specific^31^ or personal needs^32^ are likely to be more effective than completely standardised models.^29^ Key principles underpinning the study are therefore:

Active involvement of Somali parents and midwives in needs assessment and care design.Attention to language and contextual factors.Flexibility in study methods to respond to issues as they arise.A care model ready to continue or be replicated after the project concludes with only minor adjustments.

Hooyo consists of four phases with process evaluation activities informing study progress. Phase I is the preparation phase, including needs assessment, the development of contextual understanding and building a logic model for the project. Phase II includes the development of the intervention and of the evaluation tools, and phase III involves implementation and evaluation of the intervention using historical controls. In phase IV, the implementation process, the feasibility and the mechanisms of impact are evaluated, including contextual factors, using Moore’s Process Evaluation of Complex Interventions as an overarching framework.^30^ Phases I and II were conducted in 2016–2017. Recruitment and data collection for the historically controlled evaluation (phase III) and process evaluation (phase IV) commenced in late 2016 and will be completed during 2020. Women in the control group were recruited between October 2016 and April 2018 and recruitment of women into the intervention began in May 2018 and will be complete in December 2019. Final data collection will be completed by July 2020. The paper covers methodological aspects of all four phases of the study.

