### Phase III: design and methods for the historically controlled evaluation of the intervention

#### Participants and recruitment

At both sites, primiparous and multiparous Somali-born women are recruited to the study. Recruitment and retention of participants to clinical studies is a well-documented challenge in research across languages and cultures.^49^ We therefore thoroughly planned how to optimise the recruitment and information processes in relation to eligible women and adjusted processes to local prerequisites at both sites. The Somali-speaking research assistant is based at site 1 where most needed and where the majority of the recruitment is performed. In site 2, team member MA is involved with recruitment, information and data collection, supported by the Somali-speaking research assistant form site 1. All pregnant Somali-born women attending the two ANC clinics receive brief information about the study from the midwives during their first visit, and if they agree to receive further information, they are then contacted by the research assistant or MA after the first ANC visit, either by telephone or face to face for further oral and written information in Somali, English or Swedish, as needed.

Inclusion criteria are being born in Somalia and <25 weeks of gestation. Exclusion criterion is a health condition preventing participation in group antenatal care, that is, severe mental health condition or if the pregnancy care were to be transferred to a specialist obstetric clinic. During the first 18 months of the study, recruited women were included in the control group receiving standard individual care, and in the following 18 months, women are included in the intervention group. All women are informed verbally and orally about the purpose of the study and that participation is voluntary. Women included in the control group were informed that their perspectives about their care would contribute knowledge valuable for a proposed intervention study aimed at improving antenatal care for migrant women.

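### Group type coincides with clinic, so the plan can describe Somali-only and mixed groups but cannot compare them; the gANC-versus-control estimates should account for site and also be shown by site

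*Protocol article*

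**What the plan says.** The study runs in two clinics: "The intervention is implemented in two antenatal care clinics in mid-Sweden". Under Addressing language and integration, the choice of group format has two reasons. One is to respond to different local needs; the other is "to assess advantages and disadvantages with both homogeneous and heterogeneous groups regarding language and cultural background".

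The allocation follows directly: "it was decided that gANC would be offered to Somali-born women at site 1", while "At site 2, gANC would be offered to all women attending the clinic, in integrated groups". The logic model in Table 1 repeats it: "Site 1: Groups specifically for Somali-born Site 2: Groups with diverse backgrounds and languages". No clinic runs both formats.

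The format at site 2 was fitted to that clinic. Initial dialogue and choosing study settings records that "midwives reported that most Somali-born pregnant women and families were able to communicate in Swedish" and that, after discussion with the midwives, "it was agreed that integrated groups would be more appropriate and acceptable at this site". At site 1, many women were not yet fluent in Swedish. Two regular Somali interpreters were engaged there, whereas interpreters at site 2 are called in as required. The clinics also differ in setting and staffing: ten midwives in a hospital-based health centre against three in a family health centre.

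Participants and recruitment limits the evaluation to women born in Somalia, at both sites, with controls and intervention women separated by calendar period. It adds: "The Somali-speaking research assistant is based at site 1 where most needed and where the majority of the recruitment is performed". Sample size issues describes one comparison, control against gANC. It uses logistic regression for proportions and t-tests or Mann-Whitney tests for scores, and names no site term.

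**The concern.** With one clinic per format, a contrast of formats is also a contrast of clinics. A difference in satisfaction, EPDS score or attendance between sites could come from group composition. It could equally come from language fluency, settlement history, interpreter provision, staffing, setting or data collection. More women would not help, because no comparison within a clinic exists.

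Two consequences follow for the reported results.

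- The overall gANC effect is an average of two local versions with most of its weight at site 1, so it says little about mixed groups on its own. The Discussion hopes the model will transfer to other settings and migrant groups, and readers will then want to know which version produced the result.
- The controls are historical. If the two clinics differ in underlying satisfaction or EPDS, and their shares of recruitment differ between the two periods, the crude comparison moves even when gANC has no effect.

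The site 2 evidence is also one-sided. The mixed groups are open to every woman attending the clinic, but questionnaire outcomes cover only their Somali-born members.

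**Working it through.** **Step 1. What the stated sample size covers.** Inputs from Sample size issues: 65% against 82%, 80% power, alpha 20%, 70 per group, 20% loss, 174 recruited.

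- Two-sided alpha 0.20 without continuity correction: n = [1.2816·√(2·0.735·0.265) + 0.8416·√(0.65·0.35 + 0.82·0.18)]² / 0.17² = (0.800 + 0.515)² / 0.0289 ≈ 60 per group.
- With continuity correction: 72 per group, within 2 of the stated 70.
- Loss to follow-up: 140 / 0.80 = 175, against the stated 174.

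The figures reproduce closely, and they apply only to the overall control-versus-gANC comparison.

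**Step 2. Group type and site.** There are two clinics and two formats, one format per clinic, for the whole intervention period. An indicator for format and an indicator for site are the same variable. In each clinic the change between periods can be estimated, but the difference between those two changes is a site difference. It cannot be split into a format part and a clinic part.

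**Step 3. Precision by site.** The article says only that most recruitment is at site 1. I assume 100 women per period in total (its expected enrolment), with 10 to 49 of them at site 2, the 65% and 82% rates at both sites, and complete response.

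The variance term is 0.65·0.35 + 0.82·0.18 = 0.2275 + 0.1476 = 0.3751. With n2 and n1 the women per period at sites 2 and 1:

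- within site 2: half-width = 1.96·√(0.3751/n2)
- between the two sites' effects: half-width = 1.96·√(0.3751/n1 + 0.3751/n2)

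| Site 2 per period | Site 1 per period | Within site 2 | Between sites |
|---|---|---|---|
| 10 | 90 | ±38 points | ±40 points |
| 20 | 80 | ±27 points | ±30 points |
| 30 | 70 | ±22 points | ±26 points |
| 49 | 51 | ±17 points | ±24 points |

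With 70 analysed per period and a site 1 share of 50% to 90%, power to detect a 17-point difference between the two sites' effects is 21% down to 10% at two-sided alpha 0.05, and 45% down to 28% at alpha 0.20. A significant result would still be a site contrast (Step 2). No standard deviation is stated for the EPDS, so I give no matching figures for it.

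**Step 4. Shift in site mix.** If gANC has no effect, the crude difference between periods equals (change in site 1 share) × (site 1 rate − site 2 rate). Assume for illustration that the two clinics sit at the article's two rates, 65% at site 1 and 82% at site 2.

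- Site 1 share falls from 80% to 70%: (−0.10)·(−0.17) = +1.7 points.
- Site 1 share falls from 90% to 50%: (−0.40)·(−0.17) = +6.8 points.

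With an unchanged mix the distortion is zero. Stratifying by site removes it in every case.

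**The case against.** The strongest reply is that the article never promises a comparison. The sentence speaks of advantages and disadvantages with both formats, which reads naturally as description. Comparing formats is not among the specific objectives in the Introduction, and no outcome, test or sample size is attached to it. Phase IV provides session checklists, observation of group dynamics, and qualitative data from women, midwives, partners, interpreters and heads of departments. That material can describe how each format works where it is used. All of this stands, so a reader who inferred that the study fails a stated objective, or can say nothing about the two formats, would go too far. Phase IV still cannot separate format from clinic. The women for in-depth interview are identified through the study questionnaires, so on the text shown the other members of mixed groups appear not to be interviewed themselves, although observers see them and checklists cover their sessions.

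A reader might also infer that two different interventions have been pooled, or that confounding of format with site biases the gANC effect. The documents support neither. The intervention section defines one model adapted to each site, and both sites recruit to the study, so each can have its own controls. Confounding of format with site does not by itself bias gANC against control; a change in site mix between periods can.

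Two further points stand. The site 2 history of more than 25 years concerns the Somali community in the area, not the residence of individual women. An article may leave site adjustment to a fuller plan, so I do not count the absence of a site term as an error. The precision figures rest on an assumed split.

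**Conclusion.** The point holds in a limited form. Site and format are inseparable here, so the purpose given for using both formats can be met only as a description of each in its own setting, with the questionnaire view at site 2 confined to Somali-born women. This follows from the allocation and needs no numerical assumption.

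The size of the practical problem does rest on assumptions. For 49 down to 10 women per period at site 2, its own satisfaction difference would carry a 95% interval of about ±17 to ±38 points. The distortion from a shifting site mix was 1.7 and 6.8 points in the two illustrations and is nil if the mix is stable. Loss to follow-up would widen the intervals.

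For a feasibility study this is a cheap improvement in wording and reporting. It does not invalidate the evaluation.

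**What to change.** 1. Reword the purpose under Addressing language and integration as describing the feasibility and acceptability of each version of gANC in its own setting.
2. For both primary outcomes, estimate the gANC-versus-control difference with stratification or adjustment for site. For satisfaction, add site to the logistic regression. For the EPDS, use a site-stratified or site-adjusted comparison, because a plain t-test or Mann-Whitney test cannot carry site.
3. Show the same estimates by site, each against that site's own controls, labelled descriptive.
4. State that no conclusion about Somali-only versus mixed groups will be drawn from site differences, and that site 2 questionnaire results concern only the Somali-born members of mixed groups.

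Cost: a few sentences and two small tables, with no new data or recruitment. The downside is a narrower claim and wide site 2 intervals in print.
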